**3.5 Exposure**

**Definition**

All persons will be considered fully booster-vaccinated 14-days after a booster dose.

**Ascertainment**

Vaccination status, date, manufacturer and type is extracted from the study database (and linked from other sources if necessary).

Individuals will contribute pre-booster person time up to the point of booster vaccination and thereafter assigned to categories based on combinations of time since dose and booster vaccination type

Time since dose:

- pre-booster/unboosted (baseline)
- 0-13 days,
- 14-91 days,
- 92-182 days,
- 183+ days

Type of vaccine:

- mRNA XBB
- mRNA bivalent original/BA.4-5
- recombinant Beta

These categories may be assigned separate factors for different manufacturers, as required.

The following are considered ‘odd’ vaccination histories, to be considered for exclusion:

- Other vaccine types than those listed in section 3.4 above
- Vaccination between 13 February and 3 April 2023 (for Spring 23 booster analysis)
- Vaccination between 31 June and 3 Sept 2023 (for Autumn 23 booster analysis)

**3.6 Outcome(s)**

**Outcomes for Cohort Studies of Severe Disease**

Linkage with ONS mortality data, Hospital Episode Statistics (HES) and/or Secondary Uses Service (SUS), should provide the following additional outcomes:

- A COVID-19 hospitalisation will be defined as hospital admission, with
  - a primary COVID-19 discharge code present. (ICD10 U07.1, U07.2, U07.4 or U07.5)
  - a primary acute respiratory code (J04, J09-J22, J80), in conjunction with BOTH a secondary COVID-19 discharge code AND a record of a positive SARS-CoV-2 test -14 to +2 days around admission (to ensure infection prior to hospitalisation)
  - consecutive admissions with the same primary code will be aggregated and the primary hospitalisations analysis will include only stays of 2 nights or longer
- Stays of any length will be evaluated in a secondary analysis
- A very severe hospitalisation definition including use of Oxygen or admission to intensive care in addition to the primary definition above will also be evaluated in a secondary analysis.
- A COVID-19 death will be defined as a death with a COVID-19 ICD10 code on the death certificate (in any position)
- A definition including additional deaths occurring within 28 days of a positive test will also be used in a secondary analysis.

Negative controls do not need to be identified.

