**2.2 Primary objectives**

The key questions to be addressed for confirmed COVID-19 infection and clinical outcomes in 2023/24 in relation to vaccine effectiveness, taking into account previous vaccination and booster vaccination, will be to estimate:

- Overall VE by vaccine type (mRNA or other)
- VE by specific clinical risk group
- VE by time since vaccination
- VE by time period, depending on the timing of boosters and circulation of specific variants

| Outcomes combine confirmed and clinical elements:  **Confirmed**: Swab either taken   - via GP from persons presenting with COVID-like symptoms. Laboratory investigation undertaken in the PHE Respiratory Virus Reference laboratory to detect positive swab for SARS-CoV-2 and other respiratory viruses.   **Clinical:**   - COVID-19 coded hospitalisation - COVID-19 coded death - death within 28 days of positive SARS-CoV-2 test. |
| --- |

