**Table 1: Data sources for each collected variable**

| Group of Variables | Variables | Data source |
| --- | --- | --- |
| Demographic characteristics | Age on 31 August 2022 | Electronic GP record |
|  | Gender | Electronic GP record |
|  | GP practice ID | Electronic GP record |
|  | Location – NHS region | Electronic GP record |
|  | IMD quintile | Electronic GP record |
|  | Ethnicity | Electronic GP record |
| Exposure | COVID-19 vaccinations | Electronic GP record / linkage to NIMS |
|  | Dates of vaccinations | Electronic GP record / linkage to NIMS |
|  | Type of vaccine / manufacturer | Electronic GP record / linkage to NIMS |
|  | Batch numbers | Electronic GP record / linkage to NIMS |
| Outcomes TND only | Laboratory confirmed outcome | Linkage to PHE virus reference lab data |
|  | Date of swab | Linkage to PHE virus reference lab data |
|  | Date of onset | Linkage to PHE virus reference lab data |
|  | Date of receipt | Linkage to PHE virus reference lab data |
|  | Presence of fever ±10d | Electronic GP record |
|  | Presence of cough ±10d | Electronic GP record |
|  | Presence of shortness of breath ±10d | Electronic GP record |
|  | Consultation for ILI ±10d | Electronic GP record |
|  | Consultation for COVID19 ±10d | Electronic GP record |
|  | Consultation for URTI ±10d | Electronic GP record |
|  | Consultation for LRTI ±10d | Electronic GP record |
|  | Consultation for ARI ±10d | Electronic GP record |
|  | Consultation for Bronchitis ±10d | Electronic GP record |
|  | Consultation for Bronchiolitis ±10d | Electronic GP record |
|  | Consultation for asthma/COPD ±10d | Electronic GP record |
| Outcomes cohort only | Date of hospital admission | Linkage to HES / SUS data |
|  | Date of discharge | Linkage to HES / SUS data |
|  | List of ICD10 discharge codes | Linkage to HES / SUS data |
|  | Use of Oxygen | Linkage to HES / SUS data |
|  | Date of ICU admission | Linkage to HES / SUS data |
|  | Date of Death | Electronic GP record / linkage to ONS mortality data |
|  | Date of positive SARS-CoV-2 test | Linkage to SGSS / PHE virus reference lab data |
| Confounding factors | Smoking status | Electronic GP record |
|  | List of PRIMIS risk groups | Electronic GP record |
|  | Electronic Frailty Index | Electronic GP record |
|  | Indicator of living in a large residence | Electronic GP record (household key) |
|  | Cambridge Mortality Measure | Electronic GP record |
|  | Consultation count | Electronic GP record |

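### The check that infection preceded admission covers only the respiratory-code route, so hospital-acquired infections coded as primary COVID-19 are not excluded from the hospitalisation outcome

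*Protocol*

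**What the plan says.** The definition is in Section 3.6 of the COVID-19 study, under the outcomes for the cohort studies of severe disease. A hospital admission counts by either of two routes:

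- **Primary COVID-19 code.** The condition is "a primary COVID-19 discharge code present", the eligible ICD-10 codes being U07.1, U07.2, U07.4 and U07.5. Nothing further is asked.
- **Respiratory primary code.** The condition is "a primary acute respiratory code (J04, J09-J22, J80), in conjunction with BOTH a secondary COVID-19 discharge code" and also "a record of a positive SARS-CoV-2 test -14 to +2 days around admission (to ensure infection prior to hospitalisation".

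Two handling rules follow: "consecutive admissions with the same primary code will be aggregated", and "the primary hospitalisations analysis will include only stays of 2 nights or longer". Secondary analyses take stays of any length, and a very severe definition that adds oxygen use or intensive care to the primary definition.

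Section 2.2 names the endpoint simply as "COVID-19 coded hospitalisation". Section 3.1 makes hospitalisation a primary outcome of the cohort study. Table 1 in Section 3.9 lists "Date of positive SARS-CoV-2 test" among the cohort outcome variables, obtained by linkage.

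**The concern.** On the respiratory route the plan gives the purpose of the test window: infection should precede the admission. The primary-code route has no equivalent check. Both Section 3.6 and Table 1 describe the ICD-10 codes as discharge codes, so they are assigned with the whole stay in view. A patient admitted for something else who catches COVID-19 on the ward could leave with COVID-19 in the primary position. Such a stay would count even where the linked record shows a first positive well after day +2.

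An admission of that kind was not brought about by COVID-19. If boosting protects less against these events than against community-onset admission, including them pulls the estimated VE towards the lower value. Hospitalisation is a primary cohort outcome, and VE by clinical risk group and by time since vaccination are among the questions in Section 2.2, so the outcome should mean the same thing on both routes.

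**Working it through.** **Step 1: is the gap real?** The two bullets have no explicit *or* between them. They name different primary codes, so they are read here as alternatives. The other rules that could close the gap were checked in turn:

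- *Two-night minimum.* It does not address timing. A patient whose first positive is taken in hospital after day +2 has already stayed at least two nights, so the stay passes. Because the rule removes only shorter stays, it cannot lower the share of such events.
- *Aggregation of consecutive admissions.* It depends on the primary code, not on when infection occurred.
- *Any-length analysis.* It changes only the stay rule.
- *Very severe definition.* It builds on the primary definition and inherits the gap.
- *Section 3.12, cohort study.* It adds no test condition to the outcome.

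Nothing in the document applies a timing check to the primary-code route.

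**Step 2: can it be checked with planned data?** Yes, where a test is linked. Table 1 holds the admission date, discharge date, discharge codes and positive-test date for the cohort.

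**Step 3: how much could it matter?** The plan gives no figure to reproduce, so this is an illustration only. Inputs:

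- VE_c, the VE against community-onset admission: 60% and 90%, the values used in the plots in Section 3.10.
- f, the share of all baseline-group hospitalisation events that are hospital-acquired: not in the documents; assumed 2%, 5% and 10%.
- VE_h, the VE against those events: not in the documents; taken as 0%, 30% or equal to VE_c.

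Formula: VE_obs = 1 − [(1 − f)(1 − VE_c) + f(1 − VE_h)], which simplifies to VE_c − f(VE_c − VE_h).

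Example with VE_c = 60%, f = 2%, VE_h = 0%: 1 − [0.98 × 0.40 + 0.02 × 1] = 1 − 0.412 = 58.8%.

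| VE_c | VE_h | f = 2% | f = 5% | f = 10% |
|---|---|---|---|---|
| 60% | 0% | 58.8% | 57.0% | 54.0% |
| 60% | 30% | 59.4% | 58.5% | 57.0% |
| 60% | 60% | 60.0% | 60.0% | 60.0% |
| 90% | 0% | 88.2% | 85.5% | 81.0% |
| 90% | 30% | 88.8% | 87.0% | 84.0% |
| 90% | 90% | 90.0% | 90.0% | 90.0% |

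As a yardstick, Section 3.12 treats a change in VE of more than 1% as a reason to keep a covariate. Read as percentage points, f = 2% with VE_c = 60% and VE_h = 0% moves VE by 1.2 points, just past that mark. With VE_h = 30% the shift is 0.6 points, below it.

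**The case against.** The strongest reply is that the asymmetry is deliberate. The stated purpose sits inside the respiratory-code bullet and explains that bullet's own condition. There COVID-19 is only a secondary code, so its link to the admission is uncertain and a test is needed. On the other route the primary position of the code is itself the specificity condition, and Section 2.2 asks for no more than a coded hospitalisation. This is a fair reading, and it means the plan does not contradict itself. It does not settle the matter: the protocol nowhere says that a primary discharge code is taken to establish infection before admission, and it plans no check of that assumption.

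A second reply is that a booster might prevent a ward-acquired illness serious enough to be coded as primary, even though it could not have prevented the admission. That stands. A VE of zero against these events is the worst case in the table, not a finding.

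A third is that a first linked positive after day +2 does not prove acquisition in hospital. Testing may have been late, or an earlier test may not have been recorded. That also stands, and it favours a sensitivity analysis over a change to the primary definition. Such an analysis might properly be placed in a statistical analysis plan that is not at hand. If it is already there, the point is met.

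A reader might also infer three stronger things. None is supported:

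- *That hospital-acquired infections do enter the outcome.* The documents show only that they could; they say nothing on how such infections are coded or how often.
- *That these events would be dated before the infection.* The protocol lists admission, discharge and test dates but does not say which one dates the event.
- *That they fall mainly in frail, long-stay patients.* No passage says so, and the frailty index and large residence are candidate adjustment variables in Section 3.12.

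**Conclusion.** The point holds as a gap in the outcome definition. A primary COVID-19 discharge code qualifies a stay with no check that infection preceded admission, and neither the other rules nor the planned secondary analyses supply one. Hospital-acquired infections coded as primary are therefore not excluded from the primary hospitalisation outcome or from the very severe definition.

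The size is unknown. At a true VE of 60%, and with up to 10% of baseline-group events hospital-acquired, the loss ranges from nothing (equal VEs) to 6 percentage points (no effect on those events). At 90% the corresponding maximum is 9 points. Both f and VE_h are assumptions. This is a modest improvement to a definition that may be intended as written. It does not show that the hospitalisation estimates will be biased.

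**What to change.** Using the linked positive-test dates:

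1. Count, by vaccination category, the stays qualifying on a primary COVID-19 code whose earliest linked positive for the episode is later than day +2 after admission. The episode needs a defined start; the plan's own day −14 is the natural choice.
2. Report hospitalisation VE with those stays excluded, as a prespecified sensitivity analysis, and do the same for the very severe definition.
3. Keep stays with no linked test, so that events are not lost merely because testing was incomplete.
4. State in Section 3.6 why the primary-code route carries no timing condition, if that is intended.

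The alternative is to adopt the same exclusion in the primary definition.

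The cost is small: a short rule on data already linked, and an extra run of analyses that Section 4.7 describes as slow. Some community-onset cases tested late will be dropped; keeping the rule in a sensitivity analysis leaves the primary estimate untouched. Stays with no linked test remain unchecked, so the count can show the problem only among stays with a linked positive.

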**Outcomes for TND study of symptomatic GP visit**

TND requires both confirmed test positive cases and test negative controls to be identified. Both positive cases and negative controls should present to their GP with a defined set of symptoms, consistent with those required for participation in the sentinel swabbing scheme. Swabbing should be undertaken within ten days of onset of symptoms. Indications for swabbing include influenza-like illness, COVID19-like illness, acute respiratory infection, and asthma/COPD exacerbations.

A case is defined as an individual with a positive SARS-CoV-2 test via the sentinel swabbing scheme, with symptoms/illness within 10 days of onset.

A control is defined as an individual with a negative SARS-CoV-2 test via the sentinel swabbing scheme, with symptoms/illness within 10 days of onset AND (Autumn boosters only) influenza negative.

Multiple results may be available within any one individual, but a 90-day window between consecutive positive tests will be included in either study to ensure independence of positive outcomes.

Once timing of positive events have been established for the TND, the first negative result per 3 week period will be included, if at least 21 days before or 90 days after any positive result.

Analyses will initially exclude individuals presenting with asthma/COPD exacerbation, but indications for swabbing will be further explored in sensitivity analyses.

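### Hospital stays are joined only under an identical primary code although several codes qualify, so contiguous stays for one infection can count twice or, if each is under 2 nights, drop out of the primary analysis

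*Protocol*

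**What the plan says.** Section 3.1 of the COVID-19 study makes hospitalisation and death the primary outcomes of the cohort. Section 3.6 (Outcomes for Cohort Studies of Severe Disease) gives two ways for an admission to qualify:

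- Route 1: "a primary COVID-19 discharge code present. (ICD10 U07.1, U07.2, U07.4 or U07.5"), with no positive test required.
- Route 2: "a primary acute respiratory code (J04, J09-J22, J80), in conjunction with BOTH a secondary COVID-19 discharge code" and "a positive SARS-CoV-2 test -14 to +2 days around admission".

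It then fixes how stays are built and filtered: "consecutive admissions with the same primary code will be aggregated", and "the primary hospitalisations analysis will include only stays of 2 nights or longer". It adds: "Stays of any length will be evaluated in a secondary analysis". No maximum gap is given for admissions to be consecutive, and nothing is said about adjacent stays with different accepted codes.

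Further on in section 3.6, under the test-negative design (TND) heading, the protocol says "a 90-day window between consecutive positive tests will be included in either study to ensure independence of positive outcomes". Section 3.12 (Cohort study) sums person time and events over covariate levels for Poisson regression. It states neither a first-event rule nor censoring at the event.

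**The concern.** The definition accepts many primary codes for one illness but joins stays only when the code is identical. Whether one infection gives one, two or no events can then depend on how a transfer or second stay was coded, not on the disease. Two things are at stake for a primary cohort outcome. Repeat events from one infection are not independent, so the Poisson standard error is too small. And if the share of infections affected differs between boosted and unboosted person time, VE moves. The only independence window in the COVID-19 study is defined between tests, whereas route 1 needs no test.

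**Working it through.** The protocol states no figure that depends on this rule, so there is none to reproduce. The check applies the rules of section 3.6 literally to constructed histories, each a single infection.

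**Step 1: counting events.** Join stays only if they are adjacent (next admission on the same or next day, an assumption because the protocol gives no gap) and share the primary code. Then test each joined stay against routes 1 and 2, then apply the 2-night minimum. J-code stays have the secondary COVID-19 code and a positive test in the window unless stated. The last column applies the rule proposed under the fix.

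| Stays for one infection | Primary, as written | Any length, as written | Primary, after fix |
|---|---|---|---|
| U07.1 1 night, then U07.1 4 nights | 1 | 1 | 1 |
| U07.1 3 nights, then J12 4 nights | 2 | 2 | 1 |
| J18 2 nights, then U07.1 4 nights | 2 | 2 | 1 |
| U07.1 3 nights, then U07.2 3 nights | 2 | 2 | 1 |
| U07.1 1 night, then J12 1 night | 0 | 2 | 1 |
| U07.1 1 night, then J12 5 nights | 1 | 2 | 1 |
| U07.1 3 nights, home 10 days, U07.1 3 nights | 2 | 2 | 1 |
| U07.1 1 night, then J18 5 nights, no test in window | 0 | 1 | 0 |
| U07.1 1 night, then 6 nights under an unlisted primary code | 0 | 1 | 0 |

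The rule works when the code does not change (first row). It over-counts or loses the infection in rows 2 to 5. In row 7 the double count arises because no window between admissions exists.

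**Step 2: does the 90-day window help?** It acts on pairs of positive tests. A route 1 admission needs none, so the window has nothing to act on. Under route 2, one positive test can support two admissions if both fall within its window of -14 to +2 days, and again there is no second test to remove. A J-code readmission more than 14 days after that test does not qualify without a new positive, so this route is already limited.

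**Step 3: effect on precision.** Let a share d of infections be counted twice and the rest once. The ratio of true to Poisson variance is

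sum(n²)/sum(n) = [(1 - d) + 4d]/[(1 - d) + 2d] = (1 + 3d)/(1 + d).

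- d = 5%: 1.15/1.05 = 1.095; square root 1.05.
- d = 10%: 1.30/1.10 = 1.182; square root 1.09.

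**Step 4: effect on VE.** The rate ratio is multiplied by (1 + d in vaccinated)/(1 + d in unvaccinated). For an illustrative true VE of 60% (RR 0.40):

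- 5% in both groups: 1 - 0.40 × 1.05/1.05 = 60.0%.
- 10% unvaccinated, 5% vaccinated: 1 - 0.40 × 1.05/1.10 = 61.8%.
- 5% unvaccinated, 10% vaccinated: 1 - 0.40 × 1.10/1.05 = 58.1%.

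All values of d are assumptions; the documents give none.

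**The case against.** The strongest reply is that this is a narrow coding matter. Requiring the same primary code may be a deliberate choice for specificity, the 90-day sentence shows that independence was intended in both designs, and first-event rules are commonly left to a statistical analysis plan, which is not shown. Part of this stands. The words about either study do suggest that the intent reaches the cohort. A first-event restriction would remove the double counting. It would not recover the two one-night stays, because it leaves the joining rule unchanged. That rule is also not left open: section 3.6 states it.

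Four stronger readings are tempting, and the documents do not support them:

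- *Any early transfer is lost.* Loss is confined to the primary analysis, and happens only if the later stay is also under 2 nights or does not qualify. A later qualifying stay of 2 nights or longer counts once. A COVID-19-coded death after such stays still enters the separate death outcome.
- *Any readmission weeks later is a new event.* For J codes the test window largely prevents this. It holds mainly for a second stay under a primary U07 code.
- *VE is biased downwards.* A readmission after an intervening booster would be charged to boosted time, but days 0-13 after a dose are a separate category (sections 3.5 and 3.12). Only readmissions from day 14 on touch the later estimates. Overall the direction depends on which group is double counted more.
- *Stays should be joined whenever any part qualifies, dated at the first admission.* A long unrelated stay followed by a COVID-19-coded stay would then become an event dated before infection. That runs against the aim stated for route 2, that infection should precede hospitalisation.

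**Conclusion.** The concern holds in limited form. As written, contiguous stays for one infection that both qualify under different accepted codes count as two events, and two such one-night stays count as none in the primary analysis. The 90-day window does not reach route 1 readmissions. If 5-10% of patients were counted twice, the true standard error would be 1.05 to 1.09 times the Poisson one. With equal shares by vaccination status VE is unchanged; with 10% against 5%, a VE of 60% would read 61.8% or 58.1%. These sizes rest on assumed shares and on recurrent events being counted, which section 3.12 neither states nor excludes. The effect is probably modest, but it concerns a primary outcome and is easily removed.

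**What to change.** In section 3.6, replace the joining rule with wording such as: 'Admissions where discharge and the next admission fall on the same or next day, and which each meet the definition under any accepted primary code, form one stay, dated at the first qualifying admission. The 2-night minimum applies to the joined stay. At most one COVID-19 hospitalisation per person per 90 days is counted.' State also that non-qualifying stays before the first qualifying admission are not joined, so that hospital-acquired infections are neither brought in nor misdated.

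The cost is outcome-derivation code only, since admission dates, discharge dates and ICD-10 codes are already in Table 1 of the COVID-19 study. The event count falls slightly, and a true reinfection within 90 days is occasionally lost, a loss the protocol already accepts for tests. A one-night qualifying stay followed by a non-qualifying one remains outside the primary analysis (last two rows of the table); the any-length analysis still covers it.

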**3. Methods**

**3.1 Study designs**

For 2023/24 RCGP RSC and UKHSA in collaboration will use two main study designs to estimate COVID-19 vaccine effectiveness in England across all age groups, and in sub-populations for individuals registered with participating GPs in the RCGP RSC sentinel network. The primary designs to be used are as follows:

- Cohort study with primary outcomes hospitalisation and death.
- Test-negative design (TND) study on patients within the sentinel swabbing scheme.

This proposal covers both the cohort study and the TND study.

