**Cohort study**

V/E is calculated as 1- RR, where RR is the attack rate of the vaccinated group over the attack rate of the unvaccinated group.

Multivariable Poisson regression will be used with vaccination and week set as time varying covariates and all other variables set according to the individual’s status as of 1^st^ September 2022 (or 2023).

Adjustment for week of swab, age group, sex, risk-status and region (or practice) and will be included at minimum. Inclusion of additional variables including consultation quartile, IMD quintile, ethnicity, smoking status, influenza vaccination status, EFI, large residence, Cambridge Mortality Measure, will be considered individually; variables that do not impact both hospitalisation or death VE by more than 1% need not be included (i.e. the same adjustments will be made for both death and hospitalisation VE).

Vaccination status will be a time-varying categorical variable: 0-13 days post dose, 14-90 days post dose, 91-182 days post dose, with separate categories for vaccine type (and manufacturer if required). Vaccinated 6months+ ago will be the baseline category, to look at the incremental benefit of a new dose.

Person time will be calculated in days and adjusted for as an offset in the model.

The reshape and collapse commands in Stata will be used to aggregate person time and events across the levels of the time varying and fixed covariates.

Cohort analyses will be carried out for both hospitalisation and death outcomes.

Primary cohort analysis will include complete cases only, but unknown categories may be included for some missing data items.

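### The 2-night minimum stay has no exception for death, so in-hospital deaths before two completed nights are not events in the primary hospitalisation outcome or, on the natural reading, in the very severe outcome

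*Protocol*

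**What the plan says.** Section 3.6 (Outcomes for Cohort Studies of Severe Disease) defines a COVID-19 hospitalisation by discharge codes, by one of two routes. It aggregates consecutive admissions with the same primary code and adds that "the primary hospitalisations analysis will include only stays of 2 nights or longer". No exception is stated for a stay that ends in death.

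Three further provisions of 3.6 bear on the point:

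- "Stays of any length will be evaluated in a secondary analysis".
- The other secondary hospitalisation outcome is described as "A very severe hospitalisation definition including use of Oxygen or admission to intensive care in addition to the primary definition above".
- COVID-19 death is a separate outcome. It requires a COVID-19 ICD10 code anywhere on the death certificate and has no length-of-stay condition. For deaths, "A definition including additional deaths occurring within 28 days of a positive test will also be used in a secondary analysis".

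Section 3.1 describes the design as "Cohort study with primary outcomes hospitalisation and death", and section 3.12 (Cohort study) states: "Cohort analyses will be carried out for both hospitalisation and death outcomes". Table 1 in section 3.9 lists dates of admission and discharge from HES/SUS, and date of death from "Electronic GP record / linkage to ONS mortality data".

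**The concern.** A minimum stay in an outcome for severe disease appears to act as a severity threshold, on the idea that very short stays are mostly mild. But a stay can be short for two opposite reasons: quick recovery or early death. A rule that looks only at nights in hospital treats the two alike.

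The very severe outcome makes this most visible. If it carries the 2-night rule, a patient taken straight to intensive care who dies on the first night is not a very severe case, while a patient who has oxygen and goes home after two nights is.

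What is at stake is mainly whether these two outcomes measure what they are meant to measure. A secondary issue is comparison between strata. VE by clinical risk group is a primary objective (section 2.2), and the Spring 2023 analysis is restricted to people aged 75 and over and immunosuppressed people (section 3.2). If the share of admissions ending in early death differs between such groups, the rule removes a different share of severe events in each.

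**Working it through.** The protocol gives no figure for length of stay, early in-hospital death or events lost, so there is no stated number to reproduce. The check has two parts.

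**1. Apply each definition to one patient.** Take a patient who meets the hospitalisation coding and dies in hospital after 0 or 1 night.

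| Outcome (section 3.6) | Status in plan | Counted? |
|---|---|---|
| Hospitalisation, 2 nights or longer | Primary | No |
| Very severe (oxygen or ICU) | Secondary | No, if the 2-night rule carries over |
| Hospitalisation, any length | Secondary | Yes |
| COVID-19 death | Primary | Yes, if COVID-19 is on the certificate |
| Death definition adding the 28-day rule | Secondary | Yes, if certified or within 28 days of a positive test |

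Two boundary cases limit the gap. A death after exactly two nights meets the rule and is kept. Consecutive admissions with the same primary code are aggregated, so a short final stay after a transfer can still qualify.

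**2. Illustrative size.** Every input here is an assumption; none comes from the protocol. Let f be the share of early deaths among unvaccinated events in the combined outcome (stays of 2 nights or longer plus early deaths). Then

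VE_all = 1 − [(1 − f)(1 − VE_stay) + f(1 − VE_early)]

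which simplifies to VE_all − VE_stay = f × (VE_early − VE_stay).

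Take f as in-hospital mortality multiplied by the share of those deaths that fall before two completed nights:

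- Primary outcome, mortality 10–15% and early share 10–25%: f = 0.10 × 0.10 = 1.0% to 0.15 × 0.25 = 3.75%.
- Very severe outcome, mortality 30–40% and early share 15–25%: f = 0.30 × 0.15 = 4.5% to 0.40 × 0.25 = 10%.

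With VE_stay = 50% and VE_early = 70% (a gap of 20 points):

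- Primary: 0.010 × 20 = 0.2 to 0.0375 × 20 = 0.75 points, so VE_all is 50.2% to 50.8%.
- Very severe: 0.045 × 20 = 0.9 to 0.10 × 20 = 2.0 points, so VE_all is 50.9% to 52.0%.

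The VE gap drives the result as much as f does, so both are varied here (shift in percentage points):

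| f | Gap −20 | Gap 0 | Gap +20 | Gap +30 |
|---|---|---|---|---|
| 2% | −0.4 | 0 | +0.4 | +0.6 |
| 5% | −1.0 | 0 | +1.0 | +1.5 |
| 10% | −2.0 | 0 | +2.0 | +3.0 |

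The shift depends on the gap and not on the level of VE_stay: values of 40% and 60% give the same table.

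**The case against.** The strongest reply is that the plan already captures these patients. COVID-19 death is a primary outcome with no minimum stay, and the any-length analysis includes every early death that meets the coding. A reader might infer from the 2-night rule that the study's severe endpoints as a whole leave out the most severe cases. The protocol does not support that: someone who dies on the first night with COVID-19 certified is a primary event in the death analysis. This part of the reply stands and confines the point to two definitions. It does not remove it. The death outcome answers a different question (certified deaths, in or out of hospital), the any-length analysis restores early deaths only by also admitting every short non-fatal stay, and neither puts anyone back into the very severe outcome.

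Second, it is an inference that the very severe outcome carries the rule. The 2-night limit sits under the hospitalisation definition but is worded as a rule for the primary analysis. That is right. Carry-over is the natural reading, but the text does not settle it, and the ambiguity itself needs a sentence.

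Third, a reader might infer that VE is biased downward. That is not shown. VE against stays of two nights or longer is a legitimate quantity, and leaving out another event type changes what is measured. The direction depends on a VE gap for which the protocol gives no evidence. On the illustrative inputs with a 20-point gap, the primary shift is also below the 1% change in VE that section 3.12 uses to decide whether a covariate is needed. That threshold was not set for outcome definitions, but it is a fair indication of scale.

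Fourth, adding early deaths has a cost. Section 4.5 concedes that healthy-vaccinee effects cannot easily be captured, and patients who die within a night or so may be frail people in whom such effects are strong. This stands as a reason to report both versions.

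**Conclusion.** The gap is real and narrow. As written, in-hospital deaths before two completed nights are not events in the primary hospitalisation outcome and, on the natural reading, not in the secondary very severe outcome. The primary death outcome and the any-length secondary analysis are unaffected.

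Neither the size nor the direction of any effect on VE can be determined from the protocol. The illustrative shifts of 0.2 to 0.8 points (primary) and 0.9 to 2.0 points (very severe) rest on assumed mortality, an assumed early share and an assumed 20-point VE advantage against early fatal events. The very severe figure also needs the 2-night rule to carry over. The case for change therefore rests on the outcomes' validity, with no demonstrated bias behind it. It is a cheap improvement.

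**What to change.** In section 3.6, amend the rule to: stays of 2 nights or longer, or stays of any length ending in in-hospital death (date of death on or before the discharge date). State explicitly that the very severe outcome uses this amended rule or, alternatively, that it carries no stay limit. Keep the unamended 2-night definition as a sensitivity analysis, so that the effect of the change can be seen.

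The cost is one line of outcome derivation plus one extra run. Dates of admission, discharge and death are already in Table 1, so no new data are needed. The price is slightly more overlap between the hospitalisation and death outcomes, and the inclusion of some frail patients who die early.
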